## Abstract

The importance of communication skills for well-being and self-realization is widely accepted. Despite that, research on assertiveness and assertiveness training has declined significantly in recent decades. Consequently, traditional training does not consider the most recent novel technologies used to spread psychological interventions. This study proposes the development of ComunicaBene: a guided Internet-based imagery intervention to promote assertiveness. Moreover, it describes the study protocol for a randomized control trial to investigate the intervention’s efficacy and acceptability. Participants will be randomly assigned to an experimental (ComunicaBene) or waitlist control condition. ComunicaBene consists of different online training modules corresponding to three phases: psychoeducation, imaginative exposure, and in vivo-exposure. Each module provides participants with theoretical and practical content about needs, emotions, communication style, and assertiveness. Moreover, during the program, every student is supervised by a Tutor. Participants in the control condition will be included in a waiting list. Primary and secondary outcomes will include changes in assertiveness, well-being, emotional awareness, worry, and rumination. Outcomes will be assessed at pre- and post-intervention, and via a 6-month follow-up. We expect that the results will support the efficacy of ComunicaBene as an innovative, scalable, affordable, and acceptable intervention to spread assertive training through the Internet and among a broad population.

## 1. Introduction

Assertiveness includes communicating one’s needs, thoughts, and feelings clearly and directly while listening and considering the ones of others. Therefore, assertive individuals stand up for themselves without dominating the other person or letting themselves become overwhelmed [1,2]. Assertiveness can be described as a continuum, with the two extreme poles—the passive and aggressive poles—representing the absence of assertiveness and being characterized by excessive agreeableness and excessive hostility, respectively [3].

Assertiveness is a relevant factor associated with mental health and psychological well-being [4,5], self-esteem [6,7], psychological empowerment [8], the satisfaction of one’s own needs [4], and improved interpersonal relationships [9]. On the other hand, unassertiveness is a transdiagnostic factor contributing to the onset and maintenance of clinical problems [10]. For example, individuals with social anxiety often adopt passive and avoidant behaviors [11,12], repressing high levels of anger and hostility [13]. Moreover, unassertiveness correlates with depressive symptoms [5,14], contributing to both the onset and the deterioration of depressive symptoms [15,16]. Lastly, assertiveness negatively correlates with psychological distress [17]. 

Assertiveness is a skill that can be learned or improved. Assertive training aims to help individuals to change their self-perception, increase assertiveness, and reduce anxiety-based inhibitions. These interventions can stand alone or be part of more comprehensive interventions and usually include a series of cognitive and behavioral techniques, such as the behavioral rehearsal, modeling, role-playing, exposure, and cognitive restructuring [3]. Many studies suggests the effectiveness of assertive training in reducing depressive and social anxiety symptoms [18,19,20], improving communication skills [10], self-esteem [6,21], and psychological well-being [22]. 

Despite the widely accepted importance of assertiveness for well-being and self-realization, most conceptual and experimental studies about assertiveness have been published between the 1970s and 1990s. In the past decades, assertiveness training has largely disappeared as a standalone treatment. This decline could reflect the fact that research priorities moved on to other interests, such as specific mental disorders, or that assertiveness training has been integrated into more comprehensive interventions (e.g., social skill training) [10]. The decreased attention given to assertiveness in recent decades contributed to the fact that traditional assertive interventions are proposed without considering the development of recent novel technologies used to spread psychological interventions, such as Internet-based applications. 

### 1.1. The Use of the Internet to Improve Communication Skills: Advantages, Critical Issues, and Innovative Solutions

The Internet is the ultimate tool to develop and disseminate mental health interventions, as it provides a series of advantages: it can reach many people, even those that would not ask for help due to structural (e.g., high costs) and personal (e.g., fear of being stigmatized) barriers; it provides low-cost and always-accessible services for users, and it guarantees more privacy and anonymity [23,24]. Moreover, thanks to the interactive and dynamic nature of the Internet, it is possible to adjust content and graphics based on the target audience and to create online environments to ease the engagement of users [25], adding multimedia content [26,27]. A broad range of evidence supports the efficacy of Internet-based interventions, also called online or web-based intervention, in reducing symptoms related to common disorders [28,29,30,31], promoting positive mental health [32], satisfaction with life, self-esteem [33], and happiness [34], and in decreasing transdiagnostic factors [33,34,35,36,37,38]. 

Many studies included communication skills and assertiveness in more comprehensive online interventions, however in most of the studies, assertiveness is not evaluated as an outcome of the intervention, leaving the skill potential improvement unknown [39,40,41,42,43,44]. Studies that considered assertiveness as a primary outcome of the intervention reported inconsistent results, suggesting either no significant effect [36,45] or improvements in specific communication skills, but not in the general level of assertiveness [46]. 

The practice of assertive behavior is essential for the effectiveness of assertive training because it provides the opportunity to recreate a specific interpersonal situation, identify and change negative thinking patterns, evaluate irrational assumptions and expectations, decrease anxiety related to social situations [47], and enact all the appropriate behavioral responses [3]. At the same time, it is important to practice assertiveness in real-life situations, to train abilities, and to evaluate the consequences of assertive behavior [47]. This practical component of assertive training could be defective in Internet-based intervention, and it could explain the inconsistent findings of the current literature. The absence of human interactions that characterize Internet-based interventions do not guarantee supervised practice and a positive environment where the participant can interact adaptively with each other and the supervisor [48,49,50]. 

Therefore, a new approach must be found to guarantee adequate practice and foster the efficacy of Internet-based assertive interventions. We hypothesized that integrating imagery techniques within the most traditional assertive training could be an effective strategy [51]. Such a hypothesis resulted from a series of considerations. First of all, the extraordinary versatility of imagery-based techniques has been widely supported, and their effectiveness has been demonstrated both in clinical [52,53,54] and non-clinical practice [55,56]. Second of all, working with mental images provides several benefits: it allows one to experience events and their emotional consequences [57,58,59]; compared to verbal expression, mental imagery has a stronger power to evoke emotional states [60]; the neural mechanisms involved in imagination are comparable to those involved in actual perception, meaning that imagining is equivalent to act [61,62]; imagination is a behavioral and motivational booster, influencing behaviors and beliefs about the future [63]. Lastly, individuals often imagine conversing with others [64]. This specific form of imagery, called imagery interaction, allows one to experience different communication strategies, practice conversation before a real encounter, and can improve communication competence [65].

Therefore, within this background, we developed ComunicaBene: a guided Internet-based imagery training to promote assertiveness and reduce the negative emotions associated with social interactions. ComunicaBene has been designed for university students and developed on evidence-based approaches, such as Cognitive–Behavioral models, CBT [66], and the Nonviolent Communication model, NVC [67]. ComunicaBene has been developed on an e-learning platform, creating an interactive and dynamic website environment. ComunicaBene includes a series of online modules related to a specific topic (e.g., emotions, communication style, assertiveness). In particular, each module contains theoretical and practical content and multimedia materials to engage students’ attention [25]. 

### 1.2. Aim of the Present Study

The paper presents a study protocol for a randomized controlled trial to investigate the intervention’s efficacy and acceptability. In particular, we expect that ComunicaBene will effectively promote assertiveness and reduce negative emotions associated with social interactions. Moreover, a series of secondary outcomes will be considered. Especially when considering that assertiveness significantly predicts psychological well-being [68], we hypothesize a change in this dimension. Moreover, we hypothesize a change in emotional awareness, as nonassertive social functioning is significantly related to alexithymia [69]. Lastly, as worry and rumination are mostly verbal-based maladaptive emotional regulation strategies [70], we hypothesized that an increased use of mental imagery could reduce these thinking patterns [71]. The local Ethical Committee of the Department of Psychology, Sapienza University of Rome, approved the study protocol.

## 2. Materials and Methods

### 2.1. Study Design

A randomized control trial will be conducted, in which participants will be randomly allocated to an experimental or control condition. The ComunicaBene condition will consist of guided self-help imaginary training to improve assertiveness. The Waitlist, or control, condition will consist of a waiting list. Participants will receive the same intervention as those in the ComunicaBene condition but at a later time. Assessment will be run at baseline (pre-intervention assessment), at the end of the intervention (post-intervention assessment), and six months after the intervention (follow-up assessments). Please see Figure 1 for the design and participant flow chart.

### 2.2. Participants

Participants’ recruitment will be spread by word of mouth, mailing lists, and sharing fliers on various social networks (e.g., Instagram). Interested students will be invited to send an email to book their participation. ComunicaBene will be presented as imagery training to promote assertiveness, reduce the negative emotions and distress associated with interpersonal interactions, and to be able to build and maintain positive relationships. 

Eligible criteria will include enrollment in any degree course at the beginning of the study, having regular access to the Internet, the ability to write, hear, read, speak, and understand Italian, and an age between 18 and 35 years old. Exclusion criteria included the presence of a severe mental disorder (i.e., psychotic disorder, bipolar disorder) or the presence of suicidal ideation or risk.

#### Sample Size Calculation

The sample size has been estimated based on power analysis using G*Power 3.1. [72]. The following parameters were set on the sample size calculator: effect size of f = 0.21, mixed analysis of variance (ANOVA) including within-subject (3-time points), and between-subject (2 groups); effects were with 95% power and at a two-sided 5% significance level. Results suggested that the minimum required sample size was 60 participants. However, considering the percentage of drop-out occurring in Internet-based intervention for university students [73], a drop-out rate of around 25% was expected. For this reason, it is planned to recruit approximately 90 participants.

### 2.3. Measures

#### 2.3.1. Preselection Assessment

The Symptom Checklist-90-Revised, SCL-90-R [74,75], and the WHO Disability Assessment Schedule, WHODAS 2.0 [76,77] will be used to exclude the presence of a severe mental disorder or the presence of suicidal ideation or risk. The SCL-90-R is a self-report questionnaire that aims to evaluate a broad range of symptoms (i.e., somatization, obsessive compulsive, interpersonal sensitivity, depression, anxiety, hostility, phobic anxiety, paranoid ideation, and psychoticism). It also provides an index of overall psychological distress, of the intensity of symptoms, and the number of self-reported symptoms. Cronbach’s alpha for the Italian version ranges from 0.68 to 0.87. The WHODAS 2.0 is a 36-item questionnaire on a 5-point Likert scale. It allows evaluating the level of disability in six functioning domains: cognition (i.e., understanding and communicating), mobility (i.e., moving and getting around), self-care (i.e., hygiene, dressing, eating and staying alone), getting along (i.e., interacting with other people), life activities (i.e., domestic responsibilities, leisure, work, and school) and participation (i.e., joining in community activities). It provides scores for each dimension and a total score of disability. Considering the Italian version, at the domain level, reliability ranges from 0.93 to 0.96.

#### 2.3.2. Primary Outcome

Assertiveness. The Scale for Interpersonal Behavior-Short Form, s-SIB [78], will measure assertive behavior. It is a 50-item questionnaire divided into two main scales (25 items each): distress and performance, which measure the distress in state assertiveness and the probability of engaging in a specific assertive behavior, respectively. Moreover, each scale consists of five dimensions: negative assertion (i.e., requesting a change in others’ behavior, defending one’s rights and opinions, refusing requests), personal limitation (i.e., admitting one’s failures, faults, and shortcomings), initiating assertiveness (i.e., introducing oneself, starting conversations, expressing opinions), positive assertion (i.e., praising others, accepting compliments, displaying positive feelings), and general assertiveness. The Italian version showed good internal consistency with alpha coefficients ranging from 0.71 to 0.90 for the distress scale and 0.67 to 0.85 for the performance scale. 

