## 3. Statistical Analysis

SPSS (IBM) version 27 will be used to process data. Descriptive analyses will be run on sociodemographic variables, data related to the satisfaction questionnaires, and SCL-90-R and WHODAS 2.0 scores. Chi-Square tests and Student’s *t*-tests will be run to investigate differences between participants in the two conditions on baseline demographic variables, gender variables, age, and all baseline measures. If some variables significantly differ between conditions, they will be considered as covariants in the following analyses. A series of mixed models of analysis of variance (ANOVAs) will be run to investigate the efficacy of the intervention on the SIB-S, PGWBI, RRS, ARQ, PSWQ, TAS-20, and SII scores, as a function of the factor between CONDITION (ComunicaBene vs. Waitlist) and the factor within TIME (Baseline vs. Post-Intervention vs. Follow-Up). The level of significance will be set at *p* < 0.05. Effect sizes will be calculated using partial eta squared and interpreted based on benchmarks that Cohen (2013) suggested: η_p_^2^ = 0.01, small effect size; η_p_^2^ = 0.06, medium effect size; η_p_^2^ = 0.14 large effect size. The post hoc analyses of significant interaction will be conducted using the LSD post hoc test.

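### The s-SIB is the sole primary outcome, but no primary score and no one-or-both rule is named, while every ANOVA is tested at an unadjusted 5%

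*Protocol article*

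**What the plan says.** Section 2.3.2 lists one primary instrument, the s-SIB (written SIB-S in sections 2.4 and 3). Of its structure it says: "It is a 50-item questionnaire divided into two main scales (25 items each): distress and performance". It adds that "each scale consists of five dimensions", one of which is general assertiveness. It does not say which of these scores is the primary one.

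Section 1.2 gives a two-part expectation: "we expect that ComunicaBene will effectively promote assertiveness and reduce negative emotions associated with social interactions". No score, time point or success rule is attached to it.

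Section 3 plans a series of mixed ANOVAs, condition (two groups) by time (three assessments), "to investigate the efficacy of the intervention on the SIB-S, PGWBI, RRS, ARQ, PSWQ, TAS-20, and SII scores". One level covers the series: "The level of significance will be set at *p* < 0.05". A significant interaction is followed by LSD comparisons, which carry no adjustment. No multiplicity rule is given, and the s-SIB is handled in the same way as the other six instruments.

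The sample size section sizes the trial for a test at two-sided 5% with 95% power and f = 0.21. It does not say which s-SIB score this refers to.

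**The concern.** A primary outcome should lead to one identifiable conclusion with a known error rate. Here the instrument is fixed but the score is not, and the article itself sets the significance level at an unadjusted 5% for every ANOVA. Distress and performance are separate scales that measure different things, so they can give different answers. As written, authors who found an interaction on only one of them could report success on the primary outcome and remain within the plan. They could also do so for a single dimension. The 5% on which the trial was sized would then not be the error rate of the claim that is made.

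**Working it through.** **Inputs from the article.** Two main s-SIB scales with five dimensions each, so 2 × 5 = 10 dimension scores (2.3.2). Level 0.05 for each ANOVA (section 3). f = 0.21, two groups, three time points, 95% power, two-sided 5%, minimum N = 60, drop-out about 25%, about 90 to be recruited (sample size section).

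**Assumed, because the article does not state them.** Within-person correlation ρ = 0.5 and no sphericity correction (ε = 1) for the power figures. Correlation between s-SIB scores of 0, 0.3, 0.5 or 0.7 for the error rates.

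**1. The plan's own figure.** For the interaction, λ = f² × N × m / (1 − ρ) = 0.0441 × 60 × 3 / 0.5 = 15.88, with df1 = (2 − 1)(3 − 1) = 2 and df2 = (60 − 2)(3 − 1) = 116. Power at α = 0.05 is 0.950, so N = 60 is reproduced. It depends on ρ: 84 at 0.3, 72 at 0.4, 50 at 0.6 and 38 at 0.7. Allowing for drop-out, 60 / 0.75 = 80, and the planned 90 exceeds this. The calculation covers one test of one score.

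**2. Error rate if either main scale may count.** Independent scores: 1 − 0.95² = 9.75%. Correlated scores, from 400,000 simulated draws of equicorrelated normal test statistics tested two-sided: 9.4% at 0.3, 9.0% at 0.5, 8.3% at 0.7. The normal statistics stand in for the two-degree-of-freedom interaction test, so the correlated values are approximate. The independent value does not depend on the form of the test.

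**3. Worst case, any of the ten dimension scores may count.** Independent: 1 − 0.95¹⁰ = 40.1%. Correlated: 35.2% at 0.3, 28.7% at 0.5, 21.4% at 0.7. The two main scales should not be added to make twelve: general assertiveness is listed as a dimension and may be the scale total, and the article does not say.

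**4. Error rate if both main scales must be significant at 5%.** At most 5%, whatever the correlation, with no adjustment.

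**5. Power per scale under the planned ANOVA (f = 0.21, ρ = 0.5).** Expected completers: 90 × 0.75 = 67.5, taken as 67.

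| Completers | α = 0.05 | α = 0.025 (Holm's first step) |
|---|---|---|
| 60 | 0.950 | 0.913 |
| 67 | 0.969 | 0.943 |

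To keep 95% power per scale at 0.025 would take 70 completers, or 70 / 0.75 = 93.3, so 94 recruits.

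**6. Joint power if both scales must succeed, with f = 0.21 on each.** It lies between 1 − 2(1 − power per scale) and the power per scale. With 60 completers that is 1 − 2 × 0.050 = 0.90 to 0.95. With 67 it is 1 − 2 × 0.031 = 0.94 to 0.97.

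**The case against.** The best defence is that section 1.2 joins its two expectations with an *and*. If that means both scales must succeed, the 5% level holds unadjusted. This stands as a possible reading, but the sentence states an expectation and not a decision rule, and section 3 does not take it up. A separate analysis plan, not shown, could also settle the matter. That lowers the severity. It does not remove the point, because section 3 does fix the level, the model and the list of outcomes, and it does so without a rule for the two scales.

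Four stronger readings are tempting and are not supported.

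- *That no test is defined.* Section 3 defines the model, and the condition on the post hoc comparisons implies that the condition-by-time interaction is the effect of interest. What is open is the score and the success rule.
- *That all described scores share one error rate.* Counting every score in section 2.3 gives 10 + 7 + 1 + 1 + 1 + 4 + 14 = 38, and 1 − 0.95³⁸ = 86%. But sections 2.3.2 and 2.3.3 label the other six questionnaires secondary. Testing them at 5% does not raise the error of the primary outcome. It matters only if one of them is used to claim efficacy, which the article does not say will happen.
- *That all ten dimensions will be tested.* Section 3 speaks only of scores. Ten tests, and the 21–40%, are a worst case and not the stated plan.
- *That adjustment costs no power.* This would need a baseline-adjusted comparison at post-intervention, which is not the planned analysis, and a time pattern that the article does not give. If the effect is the same at post-intervention and follow-up, f² = d²/18 and d = 0.21 × √18 = 0.89 SD. If it grows linearly to follow-up, the same f means only 0.51 SD at post-intervention.

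**Conclusion.** The point holds in limited form. The primary instrument has two main scales, neither is named as primary, and nothing says whether one or both must succeed, while each ANOVA is tested at an unadjusted 5%. If either scale may count, the primary claim carries an error rate of about 8–10%, for between-scale correlations from 0.7 down to 0. This is the firmest reading of the text, because the two main scales are all that section 2.3.2 puts at the top level. The figure for ten dimensions is an upper bound on what the wording permits. Under a both-scales rule there is no inflation.

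The stated sample size of 60 reproduces with ρ = 0.5 and is not itself in error; it simply covers one test. Severity: should fix. It is a gap in wording that bears directly on the main conclusion.

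**What to change.** In section 2.3.2, name the s-SIB distress and performance main scale scores as the two primary scores; they match the two aims in section 1.2. State that the condition-by-time interaction is the primary test. In section 3, choose one rule and write it down:

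- Holm across the two scores at an overall 5%, so that success on either supports a claim for that scale; or
- both scores significant at 5%, with no adjustment.

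Label the s-SIB dimensions and the other six questionnaires as secondary or exploratory, and say that they are not a basis for the efficacy claim. This includes the SII, for which section 1.2 states no hypothesis.

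The change is to wording, made before data are seen. It has a small cost in power, which should be stated. With Holm, power per scale at the first step is about 0.94 with 67 completers and 0.91 with 60 (ρ = 0.5 assumed), against 0.97 and 0.95 at the unadjusted level. Holding 95% at that step would take about 94 recruits in place of about 90. With the both-scales rule, the cost is that joint power is below the power per scale, though not below about 0.94 with 67 completers or 0.90 with 60 if f = 0.21 applies to each.
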